## Abstract

**Background:**

Clinical guidelines for people with Parkinson’s disease (pwPD) stress that, complementary to pharmacological treatment, exercise and physiotherapy should be given a central role in disease management. Adhering to regular exercise of the right type, and with high repetition, remains a challenge for pwPD. Exergaming has the potential to increase adherence through play and personalised interventions, both in clinic and at home. Reality DTx^®^ is an augmented-reality (AR) home-based gait-and-balance exergaming intervention specifically designed for pwPD as an extension of supervised physiotherapy. The primary objective of this study is to evaluate the feasibility and potential efficacy of Reality DTx^®^.

**Methods:**

Twenty-four pwPD (Hoehn and Yahr stages 2–4) with self-reported gait and/or balance impairments will participate in this study. The study comprises a 6-week waitlist-controlled AR home-based therapeutic gait-and-balance exergaming intervention. Reality DTx^®^ will initially be prescribed remotely for a minimum of 5 days a week for 30 min per day. We will remotely set and adjust the frequency, difficulty, type of games, and/or duration weekly, based on objective and subjective data from the AR glasses and participant, respectively. In addition to the home-based gait-and-balance exergaming intervention, the study comprises three laboratory visits: before the 6-week waitlist period (t0; baseline), before the 6-week intervention period (t1; pre-intervention), and after the 6-week intervention period (t2; post-intervention). The primary study parameters are feasibility (in terms of safety, adherence, and user experience) and potential efficacy for improving gait and balance (using standard clinical gait-and-balance tests and a targeted walking-related fall-risk assessment). Recruitment started in December 2022 and the final post-intervention assessment will be according to planning in July 2023.

**Conclusions:**

This clinical feasibility trial is the first remotely prescribed and monitored home-based AR gait-and-balance exergaming intervention for pwPD. The results in terms of clinical feasibility (i.e. safety, adherence, and user experience) and potential efficacy (gait, balance, and fall-risk outcomes) form the basis for future randomised controlled studies on the effectiveness of home-based AR gait-and-balance exergaming interventions for pwPD.

**Trial registration:**

ClinicalTrials.gov, NCT05605249. Registered on 4 November 2022.

**Supplementary Information:**

The online version contains supplementary material available at 10.1186/s40814-024-01480-w.

## Background

For people with Parkinson’s disease (pwPD), gait-and-balance impairments are common and disabling. Gait impairments are varied across pwPD but are typically continuous in nature (shuffling, slow, and asymmetrical gait pattern) and can also become episodic when the disease progresses (i.e. freezing of gait) [1, 2]. Balance impairments often lead to falls related to retropulsion or stumbling, a relative inability to make sufficiently large compensatory balance-correction steps and alter body position effectively [2–4]. These motor symptoms are related to a loss of independence and a decreased quality of life [2, 5, 6].

Clinical guidelines addressing gait-and-balance impairments stress that, alongside pharmacological treatment, physiotherapy and exercise should be given a central role in disease management [7–11]. Exercise can be described as a planned, structured, repetitive, and purposeful physical activity to maintain one or more components of physical fitness, such as strength or balance [10, 12]. Different forms of exercise, ranging from isolated training of specific motor skills to multifaceted exercise like dance or boxing, have repeatedly been shown to improve both motor and non-motor symptoms [6, 12–17]. Current clinical guidelines agree that exercise interventions for pwPD should target multiple components, including gait and balance, endurance, strength, flexibility, and functional-based training like getting up from a chair [7–11], and be specifically designed for pwPD to address their motor symptoms [17].

The augmented-reality (AR) exercise intervention proposed in this clinical feasibility study protocol is specifically designed to address gait-and-balance impairments of pwPD and does that in a personalised and accessible manner. This is much needed as doing regular exercise remains a challenge for pwPD. A way to promote gait-and-balance exercise and increase adherence is to provide a personalised gait-and-balance intervention [18–20] according to the FITT principles [21] that offers exercises at the right Frequency, Intensity, of the right Type and Time (i.e. duration). Novel supporting technologies, like AR glasses, may be exploited to increase adherence by (i) providing individually tailored treatment (e.g. through the FITT principles), (ii) allowing for (online) remote monitoring of therapy adherence and performance (e.g. when delivered in a home setting), (iii) making treatment more accesible (e.g. available at any time when delivered in a home setting) and (iv) motivating users through play and instant rewarding feedback [22–25]. AR (sometimes referred to as ‘mixed reality’) is an immersive technology that merges real and digital worlds. Through AR glasses, like Magic Leap and Microsoft’s HoloLens (Fig. 1A and B), the real world can be augmented with spatial-aware digital objects (a.k.a. holograms) while—in contrast to virtual-reality (VR)—the real world remains fully visible via see-through lenses (Fig. 1C). The HoloLens has already been successfully and safely used previously in pwPD to target goal-directed movement with visual cues [26, 27]. In light of the potential of AR as an immersive technology to deliver, personalise, monitor, and promote exercises remotely at home, Reality DTx^®^ was developed by Strolll Limited [28].

**Fig. 1 Fig1:**
[figure not shown]
Augmented-reality (AR) glasses (Magic Leap 2 (**A**) and HoloLens 2 (**B**)) for performing gait-and-balance exercises at home using Reality DTx^®^ therapeutic exergames. In (**C**), ‘Smash’ is illustrated, an AR boxing game promoting weight shifts, dynamic balance, turning, and walking with direct feedback on task duration, number of required punches, and number of smashed holograms like the depicted vase)

Reality DTx^®^ is specifically designed for pwPD to improve their gait and balance, both in clinic and at home, with AR exercises being gamified, personalised, and accessible (at any time) to maximise adherence. Hence, Reality DTx^®^ can be regarded as AR therapeutic exergaming intervention, a combination of gait-and-balance exercises and gaming delivered through wearable AR glasses. Taking into account the low adherence to prescribed exercises by PD physiotherapists in standard care [20], a home-based AR gait-and-balance exergaming intervention like Reality DTx^®^ might improve the ease of accessibility to therapeutic exercises and therefore increase exercise adherence, help achieving the prescribed required number of repetitions, and potentially its effect through personalised interventions (e.g. following FITT principles), motivational feedback, and remote monitoring by the therapist.

In this clinical feasibility study, we evaluate a 6-week remotely prescribed and monitored home-based AR gait-and-balance exergaming intervention for pwPD (Reality DTx^®^). The primary objective is to evaluate its feasibility (in terms of safety, adherence, and user experience [usability and acceptability]) and potential efficacy for improving gait and balance (in terms of standard clinical and laboratory-based gait-and-balance test outcomes and targeted walking-related fall-risk indicators). The secondary objective is to examine AR glasses’ superiority (i.e. potential differences between Magic Leap 2 and HoloLens 2 subgroups) in those regards. In this study protocol, we outline the methods used to reach both objectives and discuss potential implications for future research and clinical practice.

## Methods

### Trial design

This clinical feasibility trial protocol is designed as a waitlist-controlled 6-week home-based AR gait-and-balance exergaming intervention, in which the type of AR glasses (Magic Leap 2, HoloLens 2) will be counterbalanced over participants (Table 1). All participants will start with a 6-week waitlist period, followed by the 6-week home-based AR therapeutic gait-and-balance exergaming intervention Reality DTx^®^. Baseline (t0), pre-intervention (t1), and post-intervention (t2) repeated measurements will be conducted to compare within-participant Reality DTx^®^ intervention effects against usual care (i.e. does t2–t1 differ from t1–t0?) while controlling for potential learning effects in outcomes over repeated measurements (i.e. does t1–t0 systematically deviate from 0?). Between-group comparisons will be performed to evaluate potential AR glasses superiority (i.e. does t2–t1 differ between HoloLens 2 and Magic Leap 2 subgroups)? Feasibility of the Reality DTx^®^ intervention will be examined in terms of safety, adherence, and user experience (i.e. usability and acceptability), including an evaluation of AR glasses superiority in that regard.

**Table 1 Tab1:**
[figure not shown]
Illustrates the time points, enrolment, waitlist and intervention period, and the (duration of) assessments

### Intervention

Reality DTx^®^, a class I CE marked medical device, is a software application for AR glasses HoloLens 2 and Magic Leap 2. In the proposed study, participants will follow a 6-week AR therapeutic exergaming intervention (Reality DTx^®^) comprising five complementary gait-and-balance exercises, as detailed in Table 2 (see Additional file 6 for videos of the gait-and-balance exergames). In accordance with the clinical guidelines [7–11], participants will initially be invited to use Reality DTx^®^ for 30 min per day for a minimum of 5 days a week, in their home environment. Participants are instructed that they are allowed to train more if they wish.

**Table 2 Tab2:**
[figure not shown]
Description of the five AR gait-and-balance Reality DTx^®^ exergames, including available game statistics

All five gait-and-balance games will initially be set at a 3-min duration and participants are instructed to complete them twice. The initial difficulty levels and game modes (see Table 2) will be adjusted to the participants’ gait-and-balance competence levels, as evaluated at t0 and t1. The exergaming schedule will be further personalised on a weekly basis applying shared decision-making. That is, personalisation is based on remotely monitored therapeutic exergame adherence and performance scores as well as participant-reported feedback from semi-structured weekly telephone calls (e.g. enquiring about adherence, performance, and (serious) adverse events (AE), including (near) falls and potential physical problems, as detailed below and in Additional file 3). This will result in a personalised remotely prescribed gait-and-balance exergame schedule for the next week for which frequency (number of prescribed therapeutic exergame sessions per week), intensity (by varying the difficulty level and/or game mode; see Table 2), type (type of game), and/or time (duration per game and/or therapy session) may be varied. The personalised exergaming schedule will be accessible for the participant through the AR glasses at any time during the day. Participants are free to play all prescribed gait-and-balance games in a single session or to divide them into so-called exercise snacks over the day. After finishing the prescribed exergaming schedule on a day, participants unlock bonus ‘exercise snacks’ in the so-called free-play mode, enabling participants to perform additional AR gait-and-balance exergames of their liking if they wish to. Participants receive direct feedback on gait-and-balance exergame performance during the game (e.g. number of moles hit, number of items smashed, number of buttons hit; see Table 2) and total scores upon game completion (i.e. in relation to personal high scores).

### Procedure

Duration: 12 weeks.

Study setting: Gait laboratory at the Department of Human Movement Sciences of Vrije Universiteit Amsterdam (three visits, baseline [t0], pre-intervention [t1], and post-intervention [t2]) and participants’ home environments (one home visit to set up the Wi-Fi connection for the AR glasses to be able to remotely monitor and prescribe gait-and-balance exergames, to select a safe exergaming space in the home and link this to the AR glasses and to instruct the participant how to operate, charge, and store the AR glasses, followed by 6-week independent but remotely monitored exergaming with weekly telephone calls to personalise remotely prescribed exergaming schedules).

As visualised in Fig. 2, the feasibility trial comprises:three visits to the gait laboratory to evaluate potential intervention effects vis-à-vis potential learning effects in outcomes over repeated measurements during the waitlist-control period (first laboratory visit: baseline assessment [t0], second laboratory visit: pre-intervention assessment [t1], and the third laboratory visit: post-intervention assessment [t2]),one home visit to set up the AR glasses for independent but remotely monitored usefive semi-structured telephone calls (as detailed in Additional file 3) to enquire about adherence, performance, and safety (including (serious) adverse events in relevant classes [29, 30] using questions like ‘Did you fall at any time during the training this week?’, ‘Did you nearly fall at any time during the training this week?’, ‘Did you experience any physical problems during training this week, such as dizziness, eye strain, headache or something else …’), usability (including technical issues) and perceived usefulness of the intervention, as well as to decide on the gait-and-balance exergaming schedule for the subsequent week in collaboration with the user (i.e. shared decision-making).

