#### Remote monitoring of gait-and-balance exergaming adherence and performance and telephone calls to personalise the remote prescription of exergaming schedules

The Reality DTx^®^ web portal is designed by Strolll as an online e-portal for healthcare professionals to prescribe, monitor, and adjust the Reality DTx^®^ gait-and-balance exergaming intervention and to remotely track the participant’s progress (Fig. 3). In the proposed study, the web portal will be used to remotely prescribe personalised exergaming schedules on a weekly basis (Fig. 3A) and to monitor the participant’s adherence and performance remotely (Fig. 3B, C). The initial training schedule (frequency, difficulty, type, and duration) is created by the researchers based on the supervised Reality DTx^®^ familiarisation and practice sessions during the laboratory visits (t0, t1) and home visit. The training schedule will be adjusted by the researcher every week through the Reality DTx^®^ web portal. Adjustments are made in close collaboration with the participants based on their subjective experiences evaluated during the weekly semi-structured telephone call (see Additional file 3) and based on the (objective) adherence (performed gait-and-balance exergames as a percentage of the prescribed gait-and-balance exergames) and performance (the score per game) scores available in the Reality DTx^®^ web portal. The weekly telephone calls will also be used to ask if participants experienced any technical issues (usability flags) or adverse events (safety flags).

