### Outcomes

#### Primary study parameter

The primary study parameters to evaluate the home-based AR gait-and-balance exergaming intervention are feasibility and potential efficacy:

Feasibility is expressed in:Safety, i.e. the number of (serious) adverse events categorised as falls, near falls, dizziness, eyestrain, headache, or other [29, 30] associated with the exergaming intervention, as administered during weekly semi-structured telephone calls and the Reality DTx^®^ evaluation interview. A fall is defined as a slip or trip in which one loses balance and lands on the floor, ground, or lower level [41]. A near fall is defined as a slip, trip, or loss of balance that would result in a fall if adequate recovery mechanisms were not activated [41].Adherence, i.e. compliance to the prescribed personalised exergaming intervention as measured in frequency (ratio of performed to prescribed number of exergaming sessions), time (i.e. duration, the ratio of performed to prescribed exergaming minutes per session), and repetitions (number of performed in-game functional motor tasks like number of squats, metres walked, number of functional reaches, …) as recorded in the web portal on a weekly basis throughout the 6-week Reality DTx^®^ intervention period, as well as the number of dropout participants, including reason(s) for withdrawal if specified,User experience, i.e. (1) usability based on the Dutch 26-item User-Experience Questionnaire [38] administered at t2, (2) the number and nature of the reported technological issues (e.g. AR glasses, software, Wi-Fi) during the 6-week intervention period, (3) acceptability based on a previously used intervention evaluation Likert-scale questionnaire [40] (as specified in Additional file 4) at t2, and (4) a semi-structured evaluation interview (as described previously and specified in Additional file 5) at t2 [36, 37].

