### Premature termination of the study

The study will be terminated prematurely if serious adverse events (SAE, like injurious falls) related to the Reality DTx^®^ intervention are reported for more than two participants. Liability insurance is in place in accordance with the legal requirements in The Netherlands, specifically Article 7 of the Medical Research Involving Human Subjects Act (in Dutch: Wet Medisch-wetenschappelijk Onderzoek met Mensen, WMO). This insurance provides cover for damage to research participants through injury or death caused by the study. The insurance applies to the damage that becomes apparent during the study or within 4 years after the end of the study.

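### The printed weekly safety prompts ask only about events during training, which is narrower than the safety outcome they feed; related events that start after a session are not directly asked about

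*Protocol article*

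**What the plan says.** The Procedure section describes five semi-structured calls during the six-week intervention and gives three sample safety questions. The one on falls reads "Did you fall at any time during the training this week". The one on near falls has the same form and carries the same limit to training. The one on symptoms is again tied to training: "Did you experience any physical problems during training this week, such as dizziness, eye strain, headache or something else". They are presented as examples, and the full script is in Additional file 3, which is not shown.

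Under Primary study parameter, safety is the number of (serious) adverse events by category, "associated with the exergaming intervention, as administered during weekly semi-structured telephone calls" and during the evaluation interview. The Abbreviations section defines an adverse event more widely still, as any undesirable experience during the study, related to the device or not. The stopping rule under Premature termination of the study uses "serious adverse events (SAE, like injurious falls) related to" the intervention, reported for more than two participants.

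Other routes are also stated. The Intervention section says the calls cover adverse events, "including (near) falls and potential physical problems, as detailed below and in Additional file 3". The section on remote monitoring says the calls will "ask if participants experienced any technical issues (usability flags) or adverse events (safety flags"), with no time window. The Home visit section provides a diary in which falls are noted and points for the next call may be written down. The interview after t2 includes safety among its topics.

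**The concern.** The prompts make timing a filter before anyone judges relatedness. The outcome and the stopping rule turn on association with the intervention, not on whether the event happened mid-game. Symptoms after wearing a headset, or a fall when tired after exercise, are plausible related events that may begin once the session is over.

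At stake is the completeness of a primary safety count in what the Discussion describes as unsupervised home use by people at high risk of falling. The count is also to be compared between the two headsets, which differ in weight (566 g against 260 g) and field of view. If after-effects of wear differ between devices, questions limited to the session are not well placed to show it.

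**Working it through.** The plan states no figure on this point that could be reproduced, so the check is a comparison of texts.

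**1. Window of the prompts.** All three printed prompts (3 of 3) carry the training limit. Read literally, they cover onset within an exergaming session.

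**2. Window of the outcome.** The safety parameter requires association with the intervention and sets no condition on when the event starts. The adverse-event definition requires neither association nor a session. From narrowest to widest, the order is: prompts, outcome, definition.

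**3. Coverage of categories.** The fall and near-fall prompts match two outcome categories. The third prompt names dizziness, eyestrain and headache and leaves room for anything else. Together they span every category in the outcome, so no other printed prompt asks about the same events outside a session.

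**4. What the other routes can recover.**

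- *General enquiry in the calls.* It has no session limit and, read with the wide definition, would take in post-session events. Its wording is not given. The Intervention section points to what is detailed later and to Additional file 3, so this enquiry may be the same set of questions rather than a separate one.
- *Diary.* It notes falls, but is introduced as something filled in after each session. It has no stated item for headache, eyestrain or dizziness, and is not named as a source of the safety outcome.
- *Interview after t2.* It is a named source of the outcome, but takes place once, after six weeks, so mild events rest on long recall.

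**5. Final week.** The Sample size section gives 120 calls for 24 participants: 120 / 24 = 5 each. Each call also sets the following week's schedule, and six weeks have five such transitions. The last week therefore appears to have no call of its own and rests on the interview.

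**6. Illustration only.** Let *f* be the share of related events that start after a session, and *r* the share of those recovered by the other routes. Neither is in the document; both are assumptions. If the prompts are answered literally, the share captured is 1 − *f*(1 − *r*).

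| *f* | captured if *r* = 0 | captured if *r* = 1 |
|---|---|---|
| 0.10 | 90% | 100% |
| 0.25 | 75% | 100% |
| 0.50 | 50% | 100% |

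The loss can range from nothing to *f*, and the document does not say where it lies.

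**The case against.** The strongest reply is that the operative script is not visible. The three questions are samples, the third trails off, and Additional file 3 may already ask about events between sessions. The general enquiry and the wide adverse-event definition also show that the authors did not intend to stop at the session. This stands in large part: it rules out any claim that post-session events go unrecorded. It does not remove the point about the questions the article chose to print, which are narrower than the outcome they serve.

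A second reply is that asking about any fall in this population will collect background falls. Each would need a relatedness judgement by researchers who are not blinded, with no concurrent untreated group. That is a genuine cost of the change. It is an argument for recording timing and relatedness openly rather than for leaving the selection to the wording of the question.

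A third is that the phrase about training could be taken loosely, as meaning the training week as a whole. If so, different participants may answer different questions, which is itself a reason to reword.

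Two stronger readings are tempting. A reader might infer that the safety count will be too low or that the stopping rule is compromised. The documents do not support this: other routes are stated, and a serious injury is likely to surface through the general enquiry. A reader might also set the weekly training minutes against all the minutes in a week and take the small fraction as a measure of what is missed. That is the length of the window asked about and says nothing about how many related events begin outside it.

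**Conclusion.** The point holds as a minor one. The printed prompts are limited to training, while the safety outcome and the adverse-event definition are not. Related events that begin after a session, chiefly non-serious ones such as headache, eyestrain or dizziness, are not directly elicited by those prompts. Under-reporting is possible, not demonstrated, and its size cannot be derived from the document. The conclusion assumes that the prompts are asked as printed and answered literally. If Additional file 3 already asks about events at any time between calls, the point reduces to aligning the article with the script.

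**What to change.** Reword the three items to ask about any fall, any near fall and any physical problem *since the last call*. For each event, record whether it occurred during or after exergaming and whether it is judged related to the intervention. Count only related events in the primary safety parameter. Put the same items into the existing interview after t2, so that the final week is covered in the same way as the others.

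This changes three questions in the call script and adds them to an interview already planned; it needs no extra visits, calls or staff. The downside is slightly longer calls and an unblinded relatedness judgement for each event, including background falls that the present wording would have screened out.
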